## Abstract

**Introduction:**

The goal of paediatric hand and foot burn management is hypertrophic scar and/or contracture prevention. The risk of scar formation may be minimised by integrating negative pressure wound therapy (NPWT) as an acute care adjunct as it decreases the time to re-epithelialisation. NPWT has known associated therapeutic burden; however, this burden is hypothesised to be outweighed by an increased likelihood of hypertrophic scar prevention. This study will assess the feasibility, acceptability and safety of NPWT in paediatric hand and foot burns with secondary outcomes of time to re-epithelialisation, pain, itch, cost and scar formation.

**Methods and analysis:**

This is a single-site, pilot randomised control trial. Participants must be aged ≤ 16 years, otherwise well and managed within 24 h of sustaining either a hand or foot burn. Thirty participants will be randomised to either standard care (Mepitel®—a silicone wound interface contact dressing—and ACTICOAT™—a nanocrystalline silver-impregnated dressing) or standard care plus NPWT. Patients will be reviewed until 3 months post-burn wound re-epithelialisation, with measurements taken at dressing changes to assess primary and secondary outcomes. Surveys, randomisation and data storage will be done via online platforms and physical data storage collated at the Centre for Children’s Health Research, Brisbane, Australia. Analysis will be performed using the Stata statistical software.

**Ethics and dissemination:**

Queensland Health and Griffith University Human Research ethics approval including a site-specific assessment was obtained. The findings of this study will be disseminated through clinical meetings, conference presentations and peer reviewed journals.

**Trial registration:**

Registered with the Australian and New Zealand Clinical Trials Registry (ACTRN12622000044729, https://www.anzctr.org.au/Trial/Registration/TrialReview.aspx?id=381890&isReview=true, registered 17/01/2022).

**Supplementary Information:**

The online version contains supplementary material available at 10.1186/s40814-023-01308-z.

## Article summary

Strengths and limitations of this studySecond prospective trial assessing the use of NPWT in paediatric burnsFirst randomised control trial to assess the feasibility, acceptability and safety of NPWT in paediatric hand and foot burnsFirst trial to attempt to characterise any barriers of the larger NPWT machinesPilot trial and consequently small sample size and low power for clinical outcomesTrial is based at a single quaternary centre, the generalisability of findings must therefore be interpreted in this context and with care

## Introduction

Paediatric hand and foot burns are common and can have significant therapeutic burden and morbidity [1, 2]. This is often due to hypertrophic scar and/or contracture formation; it is therefore crucial that acute burn care aims to prevent scar development. This may be achieved by reducing the time to re-epithelialisation by integrating the use of negative pressure wound therapy (NPWT) into the acute burn care model.

Isolated hand burns are the most common paediatric burn pattern, particularly in toddlers [3]. This is due to a combination of slow withdrawal reflexes, a desire to explore and a lack of higher order processing, limiting their ability to comprehend the consequences of their actions [4]. Hands are a therapeutically challenging location. Whilst the palmar hand only accounts for approximately 1% total body surface area [5], it facilitates 20 joints [6] and is functionally and cosmetically significant [7]. Paediatric foot burns, although less common, are analogous both anatomically and therapeutically to hand burns and also have a high prevalence in toddlers, who can be unaware of the dangers of hot surfaces [8].

Most hand and foot burns are superficial partial thickness, managed as outpatients and discharged without scar clinic follow-up [9, 10]. However, there is a subcohort with higher associated therapeutic burden and increased risk of morbidity. This is often due to deep, infected or larger burns—all of which decrease the likelihood of scar prevention. Prolonged times to re-epithelialisation, inpatient admissions, operative management, recurrent clinic presentations, scar clinic referrals and years of follow-up are not uncommon trajectories [11, 12]. This is due to hypertrophic scar with or without contracture formation.

A hypertrophic scar is defined as a raised scar above skin level but remains within the margins of injury [13]. These scars usually develop 2 to 3 months post-injury [13] and can be pigmented, hard and thick [14] with a loss of tissue elasticity secondary to an elastin deficiency [15]. An excess of myofibroblast differentiation can ultimately cause tissue contracture [16]. The greatest risk factor for hypertrophic scar formation is prolonged time to wound re-epithelialisation [17]. Risk factors for prolonged re-epithelialisation times include burns that are deeper, more painful, cover larger total body surface areas (TBSA), become infected and have a delayed time to presentation [18]. Hand and foot burns are more painful than burns of other locations [19]. Thus, a deep hand or foot burn with a prolonged time to re-epithelialisation would be considered high risk for hypertrophic scar formation.

Prevention of these scars is imperative as they not only carry a therapeutic burden, they also have significant and sometimes lifelong morbidity [13]. These scars can be functionally restrictive, cosmetically disfiguring, painful and itchy [20]. Fine motor skills may decrease, restricting recreational and vocational pursuits, and self-esteem may drop [21]. Ultimately, these patients may have a decreased quality of life (QoL) with significant psychosocial concerns [22]. One potential way to prevent hypertrophic scar formation is to decrease time to re-epithelialisation through NPWT.

NPWT is a device that optimises wound healing through various mechanisms including establishing a tissue pressure gradient [23], enhancing the wound bed environment, [24] micro- and macro deformations, encouraging cell mitosis [25] and promoting angiogenesis and lymphangiogenesis [26]. Our study team, led by [name] et al., completed a single-site randomised control trial (RCT) of 114 Australian children aged up to 16 years with small, superficial partial thickness paediatric burns and found that NWPT applied within the first 7 days, compared to standard dressings of Mepitel® and ACTICOAT™, decreased the time to re-epithelialisation by 22% (95% CI 7 to 34%) [27]. Through a sub-analysis, it was also identified that when NPWT was applied within the first 24 h, this group re-epithelialised faster than those who had late application [27]. We believe the benefit of NPWT is in modifying the initial progression of the zone of stasis and thus the benefit of NPWT is within the first 72 h. This is also supported by early porcine work in the 1990s [28]. We have therefore altered the application time from our first trial to application occurring within the first 24 h rather than 7 days and removed at the first dressing change—at least 72 h after application without re-application as opposed to when the burn is completely re-epithelialised. However, this study also found that the use of NPWT on paediatric patients had associated burden including the bulk of the device, mechanical issues and difficulties with school attendance. Furthermore, using NPWT on hand and foot burns was often considered inappropriate due to the perceived difficulty of application [27]. Despite this burden, clinicians believe that the burden of NPWT in paediatric hand and foot burns is outweighed by the advantage of decreasing the likelihood of hypertrophic scar formation. We have designed a pilot study to address the specific concerns from the trial by [name] and colleagues, including that hand and foot burns are not a feasible place to apply NPWT and the extent of the burden of the device.

## Methods/design

### Hypothesis and objectives

It is hypothesised that NPWT is feasible, acceptable and safe in paediatric hand and foot burns. Furthermore, it is also hypothesised that by utilising NPWT, burns will have a decreased time to re-epithelialisation and reduced pain, itch, infection and scar formation.

The primary objectives of this pilot study are to determine the feasibility, acceptability and safety of the use of NPWT in paediatric hand and foot burns. The secondary objectives will include investigating time to re-epithelialisation, pain, itch and scar formation. If further research is required, this pilot will help guide the methodology of a larger RCT. Ultimately, this study may inform the integration of NPWT into routine, acute paediatric burns care.

### Trial design

This study is a parallel-group, two-armed, single-centre, pilot, randomised trial contrasting the outcomes of burns patients treated with (1) standard dressings of Mepitel® and ACTICOAT™ (approximately 15 patients, control) against (2) standard dressings plus a NPWT RENASYS TOUCH™ device (approximately 15 patients, intervention). An overview of the study design is summarised in the Standard Protocol Items: Recommendations for Interventional Trials (SPIRIT) figure (Fig. 1) and the SPIRIT checklist (Supplement 1).

**Fig. 1 Fig1:**
[figure not shown]
Participant timeline—schedule of enrolment and data collection. DC, dressing change; POH, point of healing; NPWT, negative pressure wound therapy; TBSA, total body surface area; BBSIP, Brisbane Burns Scar Impact Profile

### Study setting

This study will be set at the Pegg Leditschke Children’s Burns Centre (PLCBC), Queensland Children’s Hospital (QCH), Brisbane, Australia. QCH is a quaternary specialist paediatric hospital with the burns centre catchment area boundaries including central and southern Queensland and northern New South Wales, an estimated area of 1,053,700 km^2^ with a population of 4.5 million people.

### Eligibility criteria

Participants will include approximately 30 children that are equal to or less than 16 years of age with a burn that is on the hand or foot (may be in the context of a larger burn and the location of the burn on the hand/foot will be recorded), managed within 24 h of sustaining the injury and is either superficial partial thickness and > 0.5% TBSA on one hand or foot or any sized burn that is deep or full thickness. The patient will be excluded if clinician treatment priority contradicts study enrolment, they do not wish to participate, the child is acutely unwell at the time of presentation or consent is unable to be confirmed within 24 h of sustaining the burn injury (Table 1).

**Table 1 Tab1:** Eligibility criteria

Inclusion criteria	Exclusion criteria
Hand or foot burn, may be in the context of a larger burn	Clinician treatment priority contradicts randomisation
≤ 16 years of age	Do not wish to participate
Managed ≤ 24 h of sustaining a burn injury	Consent unable to be confirmed within 24 h of sustaining burn injury
Superficial partial thickness burn ≥ 0.5% TBSA on one hand or foot	The child is acutely unwell at the time of presentation
Any sized burn that is deep partial or full thickness	TBSA > 10%

### Recruitment/consent

Burns Team and/or Emergency Department (ED) staff will notify researchers of eligible participants presenting to either the ED or the PLCBC. An investigator will provide the patient/family with information (both verbal and written) on the trial, and if the patient/family agrees, they will be asked to sign a consent. Where the participant does not speak English as their first language, an interpreter will be offered. A third party will be present throughout to ensure no coercion and will also sign the consent. If the family does not agree, they will be asked to consent to their baseline demographic data being included. When consenting, it is ensured that the participants/families know they have the autonomy to withdraw from the study at any stage.

Throughout the participants’ treatment, researchers will be independent of any clinical decision making processes regarding the participants. Treating clinicians will decide where the debridement occurs (i.e. theatre, ED, PLCBC) and whether it is appropriate for the patient to be enrolled in the study. Demographic data (i.e. burn details, medical, surgical and social history) will be collected before randomisation into the study.

### Intervention

For all trial patients, appropriate analgesia will be given via either a general anaesthetic or analgesia ± procedural sedation. Next, the burn will be debrided with water and QV Gentle Wash (Ego Pharmaceuticals, Sydney, Australia) and then 10 ml of 5% chlorhexidine gluconate in 500 mL of water. Patients will then have treatment according to the group they were allocated to the following.

#### Control

Participants will receive the standard dressings currently applied at the PLCBC for burns. Mepitel® (Mölnlycke Healthcare, Mikkeli, Finland) and ACTICOAT™ (Smith & Nephew, Hull, UK) will be placed over the burn and secured with Hypafix™ (BSN Medical, Hamburg, Germany). These dressings will by changed every 3 to 7 days (reflective of clinical practice) and continued until the burn is deemed re-epithelialised by the treating clinician. Data will be gathered at each dressing change.

#### Intervention

Participants will include application of the RENASYS TOUCH™ device (Smith & Nephew, Hull, UK) in addition to standard dressings. Kerlix™ AMD Antimicrobial bandage roll (CardinalHealth, Dublin, USA) is first placed as an interface between the standard dressings and NPWT device, then a Suprasorb® CNP EasyDress sleeve (Lohmann & Rauscher, Rengsdorf, Germany) applied over the standard dressing + Kerlix™ and secured with the provided film (± additional semi-permeable transparent film dressing as required to achieve seal). A small hole (< 30 mm) will be cut in the Suprasorb® CNP EasyDress sleeve over the site of the burn and a soft port applied over the hole, ensuring the hole in the EasyDress aligns with the hole of the soft port. The soft port is then attached to a cannister which is attached to the RENASYS TOUCH™ NPWT device. Suction will be applied continuously at either 80 mmHg for children > 1 years old, 60 mmHg for 6 months–1 year or 40 mmHg < 6 months old. If bilateral hands and/or feet are involved, the deeper one will have NPWT applied. If both are assessed to be of equal depth, then NPWT with a y connector will be used. The NPWT will remain on for the first 3–7 days and then removed at the first dressing change; it will not be reapplied after this. Once the NPWT is removed, treatment will continue as per the control group with standard dressings.

Throughout the trial, strategies to improve NPWT adherence will include a backpack to carry the device, dressing packs on discharge that include extra tape to help seal any leaks, education (both written and verbal) on the device and where to call to help trouble shoot issues on discharge.

Criteria for discontinuing or modifying allocated interventions for a given trial participant will include the following: on debridement of the burn, it no longer meets the eligibility criteria (i.e. burn is actually only SPT and is < 0.5% TBSA) or there is an adverse outcome requiring at least admission to the paediatric intensive care unit (PICU). Patients who become septic but are not admitted to PICU or require grafting will remain in the study.

Relevant concomitant care and interventions will include patients in the standard group receiving occupational therapy input including potential splinting from initial presentation. If required, patients in the NPWT group will only commence splinting once the NPWT is removed. The hand will be positioned in a neutral position whilst the NPWT is applied. Kerlix™, an antimicrobial crepe gauze, will aid in maintaining this position and splinting the wound whilst the NPWT is applied.

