### Assignment of interventions (randomisation)

Sequence generation will be done via a computer, automated, centralised, randomisation program hosted by the Griffith Randomisation Service. The participants will be in randomised in permutated blocks of sizes two and four so the primary investigator cannot predict the allocation sequence. The participants will be stratified based on whether they are a hand vs foot burn or whether they are being debrided in theatre vs ED. Both recruitment and randomisation will be done by the primary investigator. Once the investigator has consented the patient, they will log onto the service, enter the stratification details and a participant ID and then the group allocation will be generated.

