### Blinding

Due to the nature of the study, double blinding will not be possible as both the treating clinicians and the participant will be aware of the treatment modality. Even if NPWT were to be applied to all participants but blinded to whether the intervention has been turned on, it is evident when looking at the dressing what treatment group the participant is in. It will be possible however to blind the clinicians to some of the secondary outcomes. Time to re-epithelialisation will be calculated based on when a blinded panel of clinicians deem photographs of the wound to be 95% re-epithelialised. Similarly, scar thickness will be measured based on three blinded ultrasound photographs. In addition, to minimise bias based on observation of wound re-epithelialisation, any surveys or questions regarding the patient’s progression will be asked of staff/patients before the dressings are removed.

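### Allocation appears to be generated before debridement, which can itself show a child to be ineligible; releasing it after debridement would avoid these exits after randomisation

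*Protocol article*

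**What the plan says.** All places are in the protocol article.

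- **Assignment of interventions (randomisation).** Allocation follows consent: "Once the investigator has consented the patient, they will log onto the service, enter the stratification details and a participant ID", after which the group is generated. One stratification factor is "whether they are being debrided in theatre vs ED". "Both recruitment and randomisation will be done by the primary investigator".
- **Intervention, opening paragraph.** Analgesia and debridement are described first. Then: "Patients will then have treatment according to the group they were allocated to the following".
- **Intervention, NPWT arm subsection.** The criteria for stopping or modifying an allocated intervention include the case where "on debridement of the burn, it no longer meets the eligibility criteria". The example given is a burn that proves to be only superficial partial thickness and below 0.5% TBSA. The other criterion is an adverse outcome that needs at least PICU admission. The paragraph ends: "Patients who become septic but are not admitted to PICU or require grafting will remain in the study".
- **Recruitment/consent.** Treating clinicians decide "whether it is appropriate for the patient to be enrolled in the study". Burn details are collected before randomisation.
- **Blinding.** "both the treating clinicians and the participant will be aware of the treatment modality".
- **Table 2 and Sample size.** Ineligible children are pooled with losses and withdrawals. Table 2 sets a limit of 40% and counts only ineligibility found once treatment has begun. The sample size section assumes 20%.
- **Data analysis.** Intention-to-treat is preferred, with all children compared as randomised even after withdrawal, treatment failure or cross-over. Per-protocol analyses are added.

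**The concern.** Debridement is the point at which the true depth and area of the burn become visible. If the allocation already exists by then, a child can be randomised and found ineligible minutes later. The people making that judgement are not blinded and may already know the arm. The introduction reports that NPWT on hands and feet was often thought inappropriate in the team's previous trial, so a borderline burn might be judged differently according to the arm drawn. Even without any such influence, each exit is a departure from the randomised comparison that a different order of steps would have prevented. The pilot is meant to guide the methods of a larger RCT, so the same sequence could be carried forward.

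**Working it through.** **Step 1: the order of events.** No sentence states the order outright, so it has to be inferred.

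| Place | What it implies |
|---|---|
| Randomisation section | Allocation is triggered by consent; debridement is not named as a prior step |
| Stratification factor | Debridement site is worded as in progress or planned, not completed |
| Intervention, opening paragraph | After debridement, treatment follows a group already assigned |
| Stopping criteria | Ineligibility at debridement stops an allocated intervention; with allocation after debridement this criterion would have nothing to act on |

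All four point the same way and nothing contradicts them.

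**Step 2: do these children leave the study?** The list concerns the intervention, not follow-up. Exit is suggested only by the contrast with the sentence on who stays, and by the pooling of ineligible children with losses in the sample size section. Table 2 is weaker support. It refers to ineligibility after treatment has begun, and a child found ineligible at debridement has not yet received the allocated dressing. Exit is therefore an inference.

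**Step 3: the plan's own figures.** The protocol gives half-widths of ±11%, ±18% and ±15%. They reproduce with 1.96 × √(p(1−p)/(n−1)):

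- enrolment, p = 0.90, n = 30: 10.9%
- treatment received, p = 0.87, n = 15: 17.6%
- loss, p = 0.20, n = 30: 14.6%

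These figures are sound and do not decide the question of sequence.

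**Step 4: how many exits.** The protocol gives no rate of ineligibility at debridement, so a rate q per child is assumed, with children independent. Expected number = 30q. P(at least one) = 1 − (1 − q)^30.

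| q (assumed) | Expected of 30 | P(at least one) |
|---|---|---|
| 2% | 0.6 | 1 − 0.98^30 = 45% |
| 5% | 1.5 | 1 − 0.95^30 = 79% |
| 10% | 3.0 | 1 − 0.90^30 = 96% |
| 20% | 6.0 | 1 − 0.80^30 = 99.9% |

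The last row is an extreme: it would use up the whole 20% loss that the protocol assumes. Each exit is 1/30 = 3.3% of the sample and about 1/15 = 6.7% of an arm.

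**Step 5: imbalance by chance alone.** With 15 per arm and exits in each arm Binomial(15, q), the probability that the arms differ by two or more exits is 0.19 at q = 5% and 0.345 at q = 10%. This is chance imbalance, not bias. Any influence of knowing the arm would come on top of it.

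**Step 6: after the change.** If the allocation is released after debridement, exits after randomisation for ineligibility found at debridement fall to 0 at every q.

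**The case against.** The strongest reply is that the stopping list governs the dressing and nothing else. The data analysis section keeps children in their assigned group despite withdrawal or treatment failure, and no sentence removes anyone from analysis. The exact handling of children found ineligible after randomisation is often left to a full protocol or analysis plan, neither of which is shown. This stands. A reader might infer a flat contradiction with intention-to-treat, but the document does not support one.

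A reader might also infer that exclusions could change the verdict on the criterion that more than 80% receive their treatment. For example, 12/15 = 80.0% fails, while 12/14 = 85.7% passes. That requires the excluded child to be dropped from the denominator. Table 2 counts participants in the intervention group and gives no ground for dropping anyone, so no effect on that criterion is shown.

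Three further replies carry some weight:

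- Depth is assessed at presentation by laser Doppler and blinded photograph review, and clinicians screen before enrolment, so the number affected may be small. The article does not say, however, that these measures decide eligibility at debridement.
- A pilot may legitimately count such exits. It can still count them if they are logged before allocation.
- Feasibility results are descriptive and no formal testing is planned, which limits the harm in this trial.

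None of these replies removes the point about sequence: stopping an allocated intervention because of what debridement shows presupposes that allocation came first.

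**Conclusion.** The point holds as a minor, inexpensive improvement. On the most natural reading, the allocation is generated before the step that can show a child to be ineligible, and eligibility may then be re-judged by staff who know the arm. The exits are avoidable. Differential exclusion is a risk, not something the document demonstrates.

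The size depends on an assumed rate: 0.6 to 3.0 expected exits among 30 for rates of 2% to 10%, against zero if allocation follows debridement. The conclusion rests on the inferred order of events. Whether these children also leave follow-up or analysis is not stated, so the link to intention-to-treat is a tension that one sentence would settle.

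**What to change.** 1. Keep consent where it is. Generate the online allocation after debridement has confirmed depth and area, and before any dressing is applied. Log children found ineligible at that point as consented but not randomised. Both stratification factors are known by then and need no change.
2. State that a randomised child who meets a stopping criterion ends only the allocated dressing, and stays in follow-up, the intention-to-treat set and the safety tables. The clinical criteria themselves are unchanged.

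The cost is some protocol wording and a changed order on the day. It means a few minutes' delay, sometimes under anaesthesia or sedation. The investigator who randomises must be reachable at debridement, and an NPWT kit must be on hand for every consented child. If that proves impractical, the second change alone still protects the comparison as randomised, although it leaves the arm known when eligibility is re-judged.
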